### Strategies to improve adherence to interventions {11c}

Adherence to the intervention will be actively monitored and promoted by both the facilitators and the head teachers, who will encourage participants to attend sessions, engage with the intervention materials, and remind them about homework. Facilitators will complete documentation to track attendance and participation throughout the program. The waitlist control group will not be required to follow any specific protocol.

### Relevant concomitant care permitted or prohibited during the trial {11d}

There are no permitted or prohibited forms of concomitant care during the study.

### Provisions for post-trial care {30}

The research team will keep in contact with the schools, even after follow-up data collection. Team member [name] is a qualified clinical psychologist and will provide clinical referrals for any participants identified as needing follow-up assessment. No compensation will be provided to participants who experience harm because of trial participation.

### Outcomes {12}

All outcomes are self-report questionnaires and differences in scores will be compared from baseline (Timepoint 1), immediate post-test (Timepoint 2), and follow-up (Timepoint 3), as well as between intervention and waitlist control groups. All questionnaires will be administered at all three timepoints.

### Primary outcome measures

*Media literacy* will be assessed using the *Perceived Reality Scale–Social Media (PRS-SM)*. This questionnaire is answered on a 5-point Likert scale from *strongly disagree* (1) to *strongly agree* (5). Higher average scores indicate lower media literacy (range 1–5). The scale contains 5 items and was originally developed to focus on TV [15] and later adapted for social media by the research team. This version was validated in Spanish with Colombian adults and showed good reliability, ω = 0.84 ([name] et al., under review).*Body dissatisfaction* will be assessed using the *Body Esteem Scale for Adolescents and Adults (BESAA)*. This questionnaire is answered on a 5-point Likert scale from *never* (1) to *always* (5). Higher average scores indicate lower body dissatisfaction (range 1–5). This scale was originally validated in Canadian adults and contained 23 items [16]. The Latin American Spanish version was validated in young adults from Colombia, contains 18 items, and achieved excellent reliability, ω = 0.92 [17].

### Secondary outcomes

*Comparison attitudes* will be assessed using the *Multidimensional Physical Appearance Comparison Scale (M-PACS)*. This questionnaire is answered on a 5-point Likert scale from *never* (1) to *almost always* (5). Higher average scores indicate more frequent appearance comparisons (range 1–5). This new version is based on the *Physical Appearance Comparison Scale* [18]. Validation of both the English and Spanish versions is underway. The 14-item scale showed a two-factor structure with good psychometric properties and excellent reliability (ω = 0.91) in a sample of young Colombian adults (manuscript in preparation).*Thin ideal internalization* will be assessed using the thin internalization subscale of the *Sociocultural Attitudes Towards Appearance Questionnaire-4 (SATAQ-4)*. This questionnaire is answered on a 5-point Likert scale from *strongly disagree* (1) to *strongly agree* (5). Higher average scores indicate higher thin ideal internalization (range 1-5). The questionnaire contains 4 items [19]. The Spanish version was validated in Colombian adults [20] and yielded good reliability (Cronbach’s α = 0.87).*Girls’ Curvy*
*ideal internalization* will be assessed using the *Curvy Ideal Internalization scale* (CII). This questionnaire is answered on a 5-point Likert scale from *strongly disagree* (1) to *strongly agree* (5). Higher average scores indicate higher curvy ideal internalization (range 1–5). The original version was validated in the USA and contained 11 items [21]. The Latin American Spanish version was validated in Colombian women (*N* = 505, M_age_ = 21.48, SD = 2.96), contains 9 items, and achieved excellent reliability, ω = 0.92 ([name] et al., manuscript under review).*Boys’ drive for muscularity* will be assessed using the subscale *Muscularity-Oriented Body Image* (MBI) of the *Drive for Muscularity Scale* (DMS). This questionnaire is answered on a 6-point Likert scale from *never* (1) to *always* (6). Higher average scores indicate a higher drive for muscularity (range 1–6). The subscale contains 7 items [22]. The Spanish version was validated in adolescent boys from Spain and yielded excellent reliability (Cronbach’s *α* =.92) [23].*Eating disorder symptoms* will be assessed using the short version of the *Eating Disorder Examination Questionnaire* (*EDE-QS*), which assesses the frequency of eating disorder symptoms over the last week and contains 12 items [24]. This questionnaire is answered on a 7-point Likert scale from *0 days* (0) to *every day (6)* [7]. This version reached excellent reliability in British adults (Cronbach’s *α* =.91). We used the Spanish translation validated in adolescents from Spain [25].*General wellbeing* will be assessed using the *WHO-5 Wellbeing Questionnaire for Adolescents*, which contains 5 items [26, 27]. The questionnaire is answered on a 5-point Likert scale from *never* (1) to *all the time* (5). Higher average scores indicate higher general wellbeing (range 1–5). The Spanish version was validated in Colombian adolescents and yielded acceptable reliability, *ω* =.68 [28].

### Exploratory outcomes

We will assess *attitudes toward and interest in risky appearance-altering behaviours* in girls using the *Risky Appearance-Altering Behaviours Inventory* (RAABI). This inventory is answered on a 5-point Likert scale from *I would never want to do this* (1) to *I have done this* (5). Higher average scores indicate higher interest and more positive attitudes towards risky appearance-altering behaviours (range 1–5). This scale contains 12 items and was developed by the research team. Validation of the English and Spanish versions of the inventory is underway. The scale showed good reliability in Colombian women, *ω* =.86 ([name] et al., manuscript under review).*Colourism attitudes* will be assessed using two subscales of the Colourism Scale: self-concept and attractiveness. This questionnaire is answered on a 5-point Likert scale from *strongly disagree* (1) to *strongly agree* (5). Higher average scores reflect a greater perceived importance of skin colour (range 1–5). The questionnaire includes 8 items [29]. The scale was translated by the research team, and preliminary results showed good reliability in Colombian adults, *ω* =.85.We will assess *skin colour satisfaction* using one item: “How satisfied are you with your skin colour?” answered on a Likert scale from 1 (*not at all satisfied*) to 5 (*very satisfied*).

### Participant timeline {13}

#### Sample size {14}

The trial aims to detect small between-group effects of our outcomes. The pilot trial in Colombia (*N* = 338) showed that the smallest effect size was approximately *d* = 0.3 (body dissatisfaction in boys); we aimed for a slightly lower effect size of *d* = 0.25. For the primary sample-size calculation, we assumed a two-sided significance level of *α* = 0.05, 80% power (1 − β = 0.80), and equal allocation to two arms (intervention vs. control), yielding 251 participants per arm. Because this trial uses a cluster-randomized design, sample size calculations incorporated clustering effects, including ICC (intraclass correlation coefficient) and DE (design effect), which determines how much the sample size needs to be inflated compared to an individually randomized trial). Based on the pilot trial in Colombia, we assumed an average group size of *m* = 25 and an ICC of 0.046, which requires 529 participants per arm. We allowed for 10% attrition, yielding a sample size of 611 participants and 1250 participants in total (see Table 1 and Fig. 1).

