**Methods:**

We will recruit 1250 adolescents in 7th–10th grade (aged 11–17 years) to participate in a two-arm, cluster-randomized, open-label, controlled superiority trial in Colombia. Participating schools will be recruited by the research team. Participants will be randomized at the school level (1:1). Randomization blocks stratified by socioeconomic status (high vs. low) and geographical area (rural vs. urban) will be used to assign schools to either: (a) a school-based, four-session group intervention delivered over 2–4 weeks by trained facilitators (*n* = 625) or (b) a waitlist control group that will receive the intervention only after follow-up (*n* = 625). Participants need to be aged 11–17 years old, attending a participating school and class in grades 7 to 10, have written parental consent, and give written assent to be eligible for participation in this study. Individuals who cannot understand spoken or written language, or who do not have parental consent to participate, will be excluded. Primary outcomes are media literacy and body dissatisfaction. Secondary outcomes include appearance comparison, thin ideal internalization, curvy ideal internalization (girls only), drive for muscularity (boys only), eating disorder symptoms, and general wellbeing. Additional exploratory outcomes include risky appearance-altering behaviours (girls only), colourism, and skin colour satisfaction. Furthermore, adverse outcomes will be recorded.

Outcome assessments will happen pre-intervention (baseline; Timepoint 1), 1-week post-intervention (immediate post-test; Timepoint 2), and 9–12 months post-intervention (follow-up; Timepoint 3).

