## Methods: participants, interventions, and outcomes

### Study setting {9}

This project will run full assessments of the effectiveness of the program with adolescents attending 7th to 10th grade (typically 11–17-year-olds) in urban and rural Northern Colombia. Trained facilitators (paid research assistants) and students will deliver materials during the school day. Schools will be recruited through word of mouth and researcher contacts. All intervention activities are classroom-based and will be delivered to mixed-gender groups of 20–40 participants during class time. Outcome assessments will also be completed during the school day, in classrooms. Materials have been refined based on prior pilot study data with adolescents in the city of Barranquilla (*N* = 338). Quantitative assessments will use a wait-list control design, with outcomes measured at baseline, immediate post-test, and follow-up (9–12 months later). We are using translated and validated scales to assess body image, sociocultural internalization, eating attitudes, and general wellbeing. Additionally, we are in the process of validating scales measuring appearance comparison, curvy ideal internalization, appearance-altering behaviours, and colourism attitudes. All scales have undergone psychometric evaluation and linguistic adaptation to ensure cultural relevance for the Colombian context in a sample of Colombian adults (*N* = 505; *M*_age_ = 21.48, *SD* = 2.96, range 18–30). 

In Colombia, all areas are classified into six socioeconomic strata (*estratos*) based on residents’ income and living conditions. *Estrato* 1 includes the lowest-income households, whereas *Estrato* 6 comprises the highest. This stratification system is used to determine public service subsidies and utility fees: lower strata receive financial assistance for basic services such as electricity and water, while higher strata pay increased rates to support social equity [12].

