## Statistical methods

### Statistical methods for primary and secondary outcomes {20a}

Data will be analysed using RStudio [30]. First, data will be assessed for completely missing at random using Little’s test (MCAR) [31]. If data is missing at random (MAR), we will employ linear mixed-effects models to examine the effects of the intervention, using the Maximum Likelihood approach. If data is not missing at random, we will employ Multiple Imputation. The number of imputations will be decided based on m≈ %missing (as recommended by [32]). Furthermore, we will run MNAR sensitivity analyses (pattern-mixture/delta) [33].

Each outcome will be analysed using a linear mixed-effects model including the baseline measure of the outcome, gender, and the interaction between gender (boys vs. girls) and group (intervention vs. control) as fixed effects, along with timepoint (baseline, immediate post-test, follow-up). Random intercepts will be included for participant (to account for repeated measures) and nested clustering of classes within schools to reflect the cluster-randomized design. Analyses will be conducted separately for each outcome variable; primary outcomes will be used for confirmatory inference, while secondary and exploratory outcomes will be analysed separately with appropriate multiple-comparison adjustment as required. To estimate effect sizes, we will calculate partial eta squared. Following Cohen’s [34] guidelines, values of 0.01, 0.06, and 0.14 will be interpreted as small, medium, and large effects, respectively [34].

Subgroup analyses will be conducted based on baseline scores for each outcome variable, comparing participants with high versus low initial levels (categorized using median splits of baseline scores). In addition, moderator analyses will include interactions between each moderator and group to examine the potential influence of gender, socioeconomic status (high vs. low), location (urban vs. rural), and school type (state vs. private) on intervention effects.

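### The design effect uses a class-sized group of 25 as the cluster although schools are randomised, so the stated 80% power may not hold where a school supplies several classes

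*Protocol article*

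**What the plan says.** The Protocol article, Sample size {14}, sets the target effect ("we aimed for a slightly lower effect size of" d = 0.25) and the error rates ("we assumed a two-sided significance level of" 0.05, with 80% power), "and equal allocation to two arms (intervention vs. control), yielding 251 participants per arm". For clustering it continues: "Based on the pilot trial in Colombia, we assumed an average group size of" 25 and an ICC of 0.046, which gives 529 per arm. It then says: "We allowed for 10% attrition, yielding a sample size of 611 participants and 1250 participants in total".

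The Abstract fixes the unit of randomisation: "Participants will be randomized at the school level (1:1"). Trial design {8} and Sequence generation {16a} agree that schools are allocated. Study setting {9} says that sessions are "delivered to mixed-gender groups of 20–40 participants during class time", and Intervention description {11a} gives the same range. Eligibility covers four grades, 7 to 10. The analysis section {20a} specifies random intercepts for participants and for "nested clustering of classes within schools to reflect the cluster-randomized design".

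**The concern.** In a cluster-randomised trial the variance inflation depends on how many participants the randomised unit contributes and on how strongly they correlate. Here that unit is the school. A mean group of 25 sits within the 20 to 40 range given for a classroom group, and nothing in the article equates it with the number of participants per school. A model with classes nested in schools presupposes that at least some schools supply more than one class, because otherwise the two random intercepts could not be separated.

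If so, the calculation counts the correlation within a class but not the correlation between classes of the same school, which are all allocated together. The power statement would then describe a design that randomises classes. The trial relies on that figure to justify 1250 participants, and recruitment under Criteria for discontinuing or modifying allocated interventions {11b} runs until the planned sample size is reached. A participant count alone does not protect power if the participants come from few schools.

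**Working it through.** **Inputs from Sample size {14}:** d = 0.25 (SD 1), two-sided α = 0.05, power 80%, m = 25, ICC = 0.046, attrition 10%, 1250 in total.

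**Reproducing the plan's figures**

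- Before clustering: n = 2(1.96 + 0.8416)² / 0.25² = 251.2 per arm (stated 251).
- Design effect: DE = 1 + (25 − 1) × 0.046 = 2.104.
- After clustering: 251 × 2.104 = 528.1, rounded up to 529 (stated 529). Power at 529 per arm with this DE is 80.0%.

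The group of 25 is therefore the cluster in the calculation.

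- Attrition: 529 / 0.9 = 588, not 611. The stated figures do follow from rounding to whole groups. 529 / 25 = 21.2, so 22 groups, or 550; 550 / 0.9 = 611. Then 611 / 25 = 24.4, so 25 groups, or 625 per arm and 1250 in total. The Abstract gives 625 per arm.

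**Recalculation with the school as the randomised unit**

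With k classes of 25 per school, correlation 0.046 within a class and ρ between pupils in different classes of one school:

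DE = 1 + 24 × 0.046 + 25 × (k − 1) × ρ = 2.104 + 25(k − 1)ρ

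Participants analysed per arm: 625 × 0.9 = 562.5. Power = Φ(0.25 × √(562.5 / (2 × DE)) − 1.96).

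The article's text gives neither k nor ρ, so both are assumed: k from 1 to 4, and ρ = 0.046 (the whole ICC lies at school level), 0.023 (half of it) or 0.01.

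| Classes per school | ρ = 0.046: DE, power | ρ = 0.023: DE, power | ρ = 0.01: DE, power |
|---|---|---|---|
| 1 | 2.104, 82% | 2.104, 82% | 2.104, 82% |
| 2 | 3.254, 64% | 2.679, 73% | 2.354, 78% |
| 3 | 4.404, 52% | 3.254, 64% | 2.604, 74% |
| 4 | 5.554, 43% | 3.829, 57% | 2.854, 70% |

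Example, two classes and ρ = 0.046: 562.5 / (2 × 3.254) = 86.4; 0.25 × √86.4 = 2.324; Φ(2.324 − 1.96) = 64%.

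These are normal approximations. A t-based calculation with degrees of freedom from the number of schools, at ρ = 0.046, gives about 60%, 46% and 36% for two, three and four classes.

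**How much clustering the sample can absorb:** 562.5 / 251.2 = 2.24 is the largest DE that keeps 80% power. With two classes per school this needs ρ no greater than (2.24 − 2.104) / 25 ≈ 0.005, about one ninth of the assumed ICC.

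**The case against.** Reading 25 as a class size is an inference. The text says group size and takes it from a pilot that is not available, and neither the pilot's cluster nor the level of its ICC is stated. Analysed pupils per class may also be fewer than pupils in the room. Section {11b} contemplates switching class only when under 30% of parents consent, and the Discussion lets schools decide whether pupils without consent attend sessions. Two classes yielding 12 or 13 analysed pupils each would bring a school back to about 25 and the design effect back to 2.104.

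The planned model includes the baseline measure, which the calculation ignores. If baseline and outcome correlate at an assumed 0.5 to 0.6, equally at every level, DE is multiplied by 0.75 to 0.64. Two classes per school with ρ = 0.046 then give about 77% to 83%, and with ρ = 0.023 about 84% to 89%. At the pilot's smallest effect of d = 0.3, two classes with ρ = 0.046 give about 80% even without adjustment.

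These arguments stand as reasons why the loss may be smaller than the worst entries in the table. They do not rescue the stated calculation, which invokes none of them. With three or four classes and ρ = 0.046, the same adjustment still leaves about 64% to 70% and 54% to 60%.

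A reader might also infer that the plan gives no number of schools. That cannot be shown: the sample-size section points to Table 1 and Fig. 1, whose content was not available to this review.

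**Conclusion.** The point holds in conditional form. The calculation takes a group of 25 as its cluster, while the design randomises schools and the analysis model expects classes within them. If schools supply several classes of about 25 and pupils in different classes of a school correlate appreciably, 80% power is not delivered. Without baseline adjustment, power is then 64% to 78% with two classes, 52% to 74% with three and 43% to 70% with four, for ρ from 0.046 to 0.01. These ranges rest on assumed classes per school, an assumed level of the ICC and 25 analysed pupils per class.

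Two stronger readings are not supported. One is that power fails unless every school supplies exactly one class: about 80% survives with two classes if ρ is near 0.005, or if classes yield fewer analysed pupils. The other is that 611 and 1250 are arithmetic errors that weaken the trial: they fit whole-group rounding, which enrols more than the 588 per arm that 529 / 0.9 requires. That rounding is a minor matter of reporting.

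**What to change.** Rewrite the sample-size paragraph with the school as cluster:

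DE = 1 + (m_class − 1) × ICC_class + m_class × (classes per school − 1) × ICC_school

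- Use the expected number of analysed participants per class and per school, and give both.
- Say whether 0.046 was estimated between classes or between schools in the pilot. If only one level is known, show power over a range for the other.
- Restate the power that 1250 participants deliver. If a gain from baseline adjustment is counted, state the assumed baseline–outcome correlation.
- Add one sentence on the rounding to whole groups: 550 / 0.9 = 611, then 25 groups of 25 = 625 per arm.

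The cost is a short recalculation, mostly from pilot data already held, and one revised paragraph. The restatement itself needs no extra participants. Whether to spread recruitment over more schools is a separate and costlier decision for the sponsor once the restated power is known.

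### The design effect uses classroom-sized groups of 25 as clusters although schools are randomised, so 80% power is not assured if schools supply more than one class; the 611 and 1250 also rest on unstated rounding

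*Protocol article*

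**What the plan says.** All of the following is in the protocol article.

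- **Sample size {14}, inputs.** "we aimed for a slightly lower effect size of *d* = 0.25"; "we assumed a two-sided significance level of" 0.05; "80% power (1 − β = 0.80), and equal allocation to two arms". The result before clustering is given as "yielding 251 participants per arm".
- **Sample size {14}, clustering.** From the Colombian pilot the authors take an average group size of 25 and an ICC of 0.046, "which requires 529 participants per arm".
- **Sample size {14}, attrition.** "We allowed for 10% attrition, yielding a sample size of 611 participants and 1250 participants in total". The 611 carries no per-arm label.
- **Abstract, Methods.** "We will recruit 1250 adolescents", with 625 in each arm. Randomisation is by school.
- **Trial design {8} and Sequence generation {16a}.** Both also make the school the unit of allocation.
- **Study setting {9} and Intervention description {11a}.** The intervention is delivered to classroom groups of 20 to 40.
- **Statistical methods {20a}.** Random intercepts are planned for participant and for classes nested within schools.

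**The concern.** Two things stand out. First, the printed steps do not connect: 529 with a 10% allowance does not give 611, and doubling 611 does not give 1250. A reader cannot tell from the paragraph how the target was reached.

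Second, the size of 25 matches the classroom group, not the school. A design effect for a cluster-randomised trial has to reflect all pupils who share a randomised unit. If a school supplies several classes, pupils in different classes of that school were allocated together, and any correlation between them inflates the variance further. The analysis model allows for both levels, but the sample-size formula has room for only one. What is at stake is the stated 80% power. {11b} keeps recruitment open until the planned sample size is reached, so this paragraph sets the enrolment target.

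**Working it through.** **Inputs.** From {14}: d = 0.25, two-sided alpha 0.05, power 0.80, 1:1 allocation, m = 25, ICC = 0.046, attrition 10%. From the Abstract: 625 per arm. Power below uses the normal approximation, Φ(0.25 × √(n_eff/2) − 1.96), where n_eff is the effective number per arm.

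**1. The plan's own figures.**

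- Before clustering: 2 × (1.960 + 0.842)² / 0.25² = 251.16, printed as 251.
- Design effect: 1 + (25 − 1) × 0.046 = 2.104.
- After clustering: 251 × 2.104 = 528.1, rounded up to 529. This matches.
- Attrition applied directly: 529/0.90 = 587.8, so 588 per arm and 1176 in total. The multiplicative version, 529 × 1.10, gives 582. Neither is 611.
- Attrition after rounding to whole groups: 529/25 = 21.2, so 22 groups = 550, and 550/0.90 = 611.1. This matches 611.
- Rounding again: 611/25 = 24.4, so 25 groups = 625 per arm and 1250 in total. This matches the total and the Abstract's arms.

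The rounding is inferred from the numerical match; the article does not state it.

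**2. Power on the plan's own inputs.** 625 × 0.90 = 562.5 per arm at follow-up, and 562.5/2.104 = 267.3 effective. Power is 82.4%. With 588 per arm it would be 80.1%.

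**3. Power with schools as the randomised unit.** Neither the number of classes per school nor a between-class correlation appears in the text shown, so both are assumptions here. Take 0.046 as the correlation between pupils in the same class, two classes of 25 per school, and ρ as the correlation between pupils in different classes of the same school. Then

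DE = 1 + 24 × 0.046 + 25 × ρ = 2.104 + 25ρ.

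| ρ | DE | 562.5/DE | Power |
|---|---|---|---|
| 0 | 2.104 | 267.3 | 82.4% |
| 0.005 | 2.229 | 252.4 | 80.2% |
| 0.01 | 2.354 | 239.0 | 78.0% |
| 0.02 | 2.604 | 216.0 | 73.8% |
| 0.046 | 3.254 | 172.9 | 64.2% |

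The largest design effect that still gives 80% power is 562.5/251.16 = 2.240, so the limit is ρ = (2.240 − 2.104)/25 = 0.0054. The last row is the case where 0.046 applies to the whole school of 50 pupils.

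**4. Sensitivity to how attrition is handled.** The table keeps 25 pupils per class, as the plan's formula does. If 10% loss also reduces each class to 22.5, then DE = 1 + 21.5 × 0.046 + 22.5ρ = 1.989 + 22.5ρ. The limit moves to (2.240 − 1.989)/22.5 = 0.011. Power is then 80.4% at ρ = 0.01, 76.6% at 0.02 and 67.4% at 0.046.

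**The case against.** The strongest reply is that nothing is miscalculated. One simple rule, rounding up to whole groups of 25, returns both 611 and 625. The Abstract shows that 1250 is 2 × 625, and the preceding sentence gives 529 as per arm, so the meaning of 611 is clear in context. A journal article may leave out rounding steps, and the total exceeds the 1176 from direct division. All of this stands. A reader might infer that the sample-size basis is wrong, or that the plan really allows for 13.4% loss (1 − 529/611). The documents do not support either reading: the stated 10% reproduces every figure once the rounding is applied.

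On the cluster unit, the reply is that the article openly calls 25 a group size, that the pilot ICC might already be a school-level value, that a school might supply only one class, and that the number of schools may be given in Table 1 or Fig. 1, which are not shown. This stands in part. With one class per school, the 82% holds. But the paragraph does not say which unit m and the ICC describe. A planned model with classes nested within schools only makes sense if at least some schools supply more than one class.

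A reader might also infer that the trial is underpowered, at 64% say. The documents do not show that. The figure assumes 50 pupils per school and an unchanged ICC, and a correlation across classes of a school is often lower than within a class.

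**Conclusion.** The point holds in two parts of unequal weight.

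The attrition step is a reporting gap only. The printed steps skip two roundings and 611 lacks its label, but no power is lost.

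The cluster unit is the substantive part. The only chain found that reproduces the figures treats groups of 25 as independent clusters, 25 per arm, in a trial that randomises schools. If schools supply more than one class and 0.046 is a within-class ICC, 2.104 understates the inflation. With two classes per school, the margin above 80% is used up at a between-class correlation of about 0.005, or about 0.011 if attrition also shrinks the classes. The conclusion is therefore that the stated 80% power is not assured, not that it is shown to be missed. It rests on the assumed two classes per school and the assumed level of the ICC; more classes per school would tighten the limit.

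**What to change.** Reword the Sample size paragraph:

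1. Label 611 as per arm and show the rounding: 529, up to 22 groups of 25 = 550; 550/0.90 = 611 per arm; up to 25 groups = 625 per arm; 1250 in total.
2. Say whether m = 25 and ICC = 0.046 refer to the class or the school.
3. Recompute the design effect with the planned pupils and classes per school, including a between-class, within-school correlation with a stated source or range.
4. Restate the power that 1250 delivers with schools as the randomised unit.

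Do not repair the chain by restarting from 252 or 253 per arm. That gives 531 to 533 after the design effect and 590 to 593 after attrition, and 593/25 = 23.7 rounds up to 24 groups, which is 600 per arm and not 625.

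The cost is one paragraph and a short recalculation. Enrolment does not change on this ground, though the restated power may be lower than 80%.
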